### Inclusion and exclusion criteria

Mothers and children are eligible for inclusion if they meet the following criteria: child included in the original NELLI cohort, child age of 4–7 years, the possibility of using a DVD player or the content behind a YouTube-link, and ability to perform PA and use the accelerometer as instructed. Mothers and children who because of medical factors (for example, chronic diseases, musculoskeletal or bone disorders, need for special rehabilitation, or trauma) are unable to perform PA will be excluded. Eligibility and willingness to participate in the research will be assessed via interviews of the participants during the personal contact of sampling for the NELLI study.

### Recruitment of the study population and randomization

Participants (i.e., mother-child pairs) in the Moving Sound study are being recruited from the cohort of the NELLI five-year follow-up study, which is based on the original cohort from the NELLI study (*n* = 837). The focuses of the NELLI work have been prevention of type 2 diabetes, metabolic syndrome, and obesity. The protocol and methods of the original NELLI study have been reported upon in detail previously [23].

All NELLI follow-up study participants will be offered an opportunity to be part of the Moving Sound study. Mother-child pairs are being invited from 14 municipalities in the Pirkanmaa area, in south-western Finland, via an information letter and phone call. We expect to recruit 30–40 % of the original NELLI cohort (again, *n* = 837), for 251–335 mother-child pairs, in all. This expectation is based on figures from the original NELLI study, wherein 640 women agreed to participate and 399 women completed the intervention [24, 25]. Possible reasons for dropping out at this stage could include participants being unable to be reached or unwilling to take part in the study. Estimate of sample size and randomization for the study are shown in Fig. 1.

**Fig. 1 Fig1:**
[figure not shown]
Flow chart, estimates for sample size, and randomization for the study

For the randomization, there was not an appointment order list and the total number of participants was unknown. Randomization was performed for blocks of four participants, in a 2:2 ratio: two mother-child pairs in the intervention group for two pairs of control participants. In practical terms, four random numbers were generated, and the pairs associated with the two largest were assigned to the experimental group and the two lowest to the control group. For allocation of participants, an appointment order list for the NELLI five-year follow-up study is being used. Mothers are randomized to the intervention or control group by means of sealed envelopes in the contact for sampling for the NELLI study.

The recruitment started in November 2014 and will continue until December 2015. Because season-to-season changes in Finland are large (with cold and snowy winters, rain in the spring and fall, and a warm summer), seasonal differences in PA levels may present themselves [26, 27]. Though the intervention takes place in the home, we have paid attention to this effect by performing the intervention throughout the year.

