**Methods:**

Mother-child pairs (child age of 4–7 years) will be recruited from among NELLI lifestyle-modification study five-year follow-up cohort participants, encompassing 14 municipalities in Pirkanmaa region, Finland.

Accelerometer and exercise diary data are to be collected for intervention and control groups at the first, second and eighth week after the baseline measurements. Background factors, physical activity, screen time, motivation to exercise, and self-reported height and weight, along with quality of life, will be assessed via questionnaires. After the baseline and first week measurements, the participants of the intervention group will receive a movement-to-music video program designed to reduce sedentary time and increase physical activity. Intervention group mother-child pairs will be instructed to exercise every other day while watching the video program over the next seven weeks. Information on experiences of the use of the movement-to-music video program will be collected 8 weeks after baseline. Effects of the intervention will be analyzed in line with the intention-to-treat principle through comparison of the changes in the main outcomes between intervention and control group participants. The study has received ethics approval from the Pirkanmaa Ethics Committee in Human Sciences.

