## Outcome measurements and pre-testing

### Outcomes

**The main objective** of the study is to decrease SB and increase PA among the mothers and their children by means of the movement-to-music video program.

**The primary outcomes** of the study are SB and PA, which will be assessed objectively by means of the accelerometer and further examined via the exercise diaries and questionnaires. Measurements will be performed in the first, second and eighth weeks of the intervention. For inclusion in the analysis, accelerometer data for at least four days per week and measurement time of more than 10 h per day will be needed. Participants using the accelerometer on fewer than four days per week will be excluded. Any participants whose measurement time for a given day is over 20 h will be considered to have slept with the accelerometer. To avoid possible bias in SB time, the recording time for them will be capped at 20 h, with the deduction coming from their lying-down time. The measurement discriminates among the time spent in a sitting or reclining posture, standing still, and PA. The daily amount of standing-up (breaks in sedentary time) will be calculated from the number of lying/sitting periods that end with standing. Lying, sitting, and standing time, along with light, moderate, and vigorous PA time during waking hours, will be analyzed both in minutes and as a proportion of the measurement time (at least 10 h per day). In the analysis, moderate and vigorous activity might be combined as MVPA if vigorous PA covers a very small proportion of the total measurement time.

**Secondary outcomes** of the study include the quantity of self-reported sitting and screen time among mothers and children, motivation to exercise, and the motivational quality of the music and movement-to-music video. Additional secondary outcomes are mother’s weight and quality of life, depression, anxiety, perceived health, and work ability assessed by a questionnaire.

**The specific aim** is to study the effectiveness of the intervention by comparing accelerometer use alone with a combination of accelerometer and movement-to-music video program for mother-child pairs.

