### Data collection

The baseline data collection (with body-weight and questionnaire-based measurement) will take place during the personal contact of sampling for the NELLI study. Information on the accelerometer-based measurements will be supplied to participants at the same time. The timing of the data collection related to these measurements, the exercise diaries, and the questionnaires is described in detail in Table 3.

**Table 3 Tab3:** Moving Sound data collection and measurements at baseline and the 1st, 2nd, and 8th week after baseline measurement

Data collection	Baseline	1st week	2nd week	8th week
Measurements and exercise diaries				
Accelerometer measurements		X	X	X
Exercise diaries		X	X	X
Weight	X			
Questionnaires				
Background questions	X			
Weight		X	X^a^	X
Earlier physical activity (LTPA)	X			
Current physical activity and sitting time	X		X^a^	X
Motivation to exercise (EIS and TPB)	X		X^a^	X
Quality of life (15 D)	X			
Depression (BDI)	X			
Anxiety (SAI)	X			
Work ability	X			
Perceived health	X			
Mother's musical background			X^a^	
Motivational quality of the music			X^a^	
Other motivation-related factors			X^a^	X^a^
Experiences of use of the video			X^a^	X^a^
Perceived changes in PA			X^a^	X^a^

^a^Intervention group

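### Randomization comes before the week-1 accelerometry, the only pre-video measurement of the primary outcome, and nothing stated withholds the allocation until that week is over

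*Protocol article*

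**What the plan says.** All references are to the protocol article.

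- **Randomization** (Recruitment of the study population and randomization): "Mothers are randomized to the intervention or control group by means of sealed envelopes in the contact for sampling for the NELLI study".
- **What that contact collects** (Data collection): "The baseline data collection (with body-weight and questionnaire-based measurement) will take place during the personal contact of sampling for the NELLI study". On the accelerometers: "Information on the accelerometer-based measurements will be supplied to participants at the same time". Table 3 has no accelerometer mark in the Baseline column; the first is under the 1st week.
- **Accelerometer weeks** (Abstract, Methods): "Accelerometer and exercise diary data are to be collected for intervention and control groups at the first, second and eighth week after the baseline measurements".
- **Release of the video** (Abstract, Methods): "After the baseline and first week measurements, the participants of the intervention group will receive a movement-to-music video program". The section on the interventions also puts delivery of the DVD and link at the end of the first week.
- **Primary outcomes** (Outcomes): sedentary behavior and physical activity, "which will be assessed objectively by means of the accelerometer and further examined via the exercise diaries and questionnaires". The same section requires at least four days of data per week, with more than 10 h per day, and excludes participants with fewer than four days.
- **Analysis** (Statistical methods): intention-to-treat comparison of changes between groups, by linear regression.

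**The concern.** A reference value for change should be recorded before group membership can influence it. Here the outcome is how much mothers and children sit and move, and no blinding is described. A mother who knows that a movement video is coming may start moving more in the week before it arrives, or may put off activity until it does. A mother who knows that she is a control may wear the device less carefully. Either would make week 1 differ between arms for reasons other than chance, and that difference would pass into the change.

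The wear rule adds a second route. A pair whose week-1 record falls short of four valid days leaves the analysis after being randomized. If wear depends on knowing the group, this loss is unequal between arms, which sits badly with the stated intention-to-treat principle.

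**Working it through.** **Order of events.** Putting the sections together gives:

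1. NELLI sampling contact: weight, questionnaires, accelerometer information and randomization by envelope.
2. Week 1: accelerometer worn, no video.
3. End of week 1: intervention group receives the video.
4. Weeks 2 and 8: accelerometer worn again.

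Step 2 is the only accelerometry before the video, and it follows step 1. No sentence keeps the envelope closed, or the result undisclosed, between steps 1 and 3.

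**Reproducing Table 1.** The inputs are α = 0.05 (two-sided reproduces the table), power 80 %, and the stated means and SDs. Per group, n = 2 × (1.960 + 0.842)² × (SD/difference)².

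- 25 min, SD 70: 123.1, rounded up to 124, as stated.
- 30 min, SD 60: 62.8, rounded up to 63, as stated.

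The four rows between also reproduce (107, 91, 86, 74).

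**Hypothetical effect of a week-1 shift.** Suppose that knowing the group lowers intervention-arm sedentary time in week 1 by *s* min/day. The documents give no value for *s*. Table 1's SD of 70 is used as the SD of change, which is also an assumption.

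Change in the intervention arm = 435 − (460 − s); change in the control arm = 0; so the apparent contrast = 25 − s.

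Power = Φ(contrast / (SD × √(2/n)) − 1.96). With n = 124 and SD = 70, the standard error is 8.89.

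| Week-1 shift in intervention arm | Contrast (min) | Power |
|---|---|---|
| none | 25 | 80 % |
| 5 min fall | 20 | 61 % |
| 10 min fall | 15 | 39 % |
| 5 min rise | 30 | 92 %, effect overstated |

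For the other end of Table 1 (30 min, SD 60, n = 63), falls of 0, 5 and 10 min give 80 %, 65 % and 46 %. A 5-min rise gives a contrast of 35 min and 91 %.

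**With baseline-adjusted regression.** Let ρ be the assumed correlation between week 1 and week 8, with SD 70 at both times. The contrast becomes 25 − ρs and the residual SD is 70 × √(1 − ρ²). At ρ = 0.5 the SD of change is 70 × √(2 × 0.5) = 70, which matches the table above, and the residual SD is 60.6. Power is then 90 % with no shift, 83 % with a 5-min fall (contrast 22.5) and 74 % with a 10-min fall (contrast 20). At ρ = 0.7 (residual SD 50.0) a 10-min fall leaves a contrast of 18 and 81 % power. Adjustment reduces the bias from s to ρs but does not remove it.

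**Week-8 values alone.** The contrast is 435 against 460, untouched by *s*. With SD 70 and 124 per group its power is 80 %, the calculation that Table 1 presents.

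**The case against.** The best reply is that disclosure is inferred. A reader might conclude that mothers certainly know their group during week 1. The article says only that they are randomized by envelope at the contact; it does not say that they are told then. Figures 1 and 2, which could refine the timing, are not shown. This stands: the supportable statement is that randomization precedes week 1 and nothing stated withholds the result.

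The outcome is device-measured and the video is not in hand during week 1, so any effect is limited to anticipation, wear and dropout. This also stands, and it limits the likely size.

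A reader might take the fall to 39 % as the expected loss. It needs an unsourced 10-min shift, an assumed SD of change and a pure change score. Statistical methods names linear regression without saying whether the week-1 value is a covariate. The figure is one hypothetical case.

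Three further inferences are tempting but do not carry weight:

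- *The outcome section counts week 1 within the intervention* ("Measurements will be performed in the first, second and eighth weeks of the intervention"). Both arms wear the accelerometer, and the control arm is defined by it, so the phrase can cover the whole eight weeks. The video's timing is clear elsewhere.
- *The two remarks on an appointment order list contradict each other.* They can be read as two stages: no list when the sequence was generated, and a list in use now for allocation.
- *The envelopes are predictable* ("Randomization was performed for blocks of four participants, in a 2:2 ratio"). Across the six possible orders of a block, 8 of 24 positions are fixed by the earlier ones, but only for someone who knows the block size and tracks every allocation. The article says neither. Varying the block size is an optional refinement.

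**Conclusion.** The point holds in a limited form. As written, the only reference value for change in the primary outcome is a post-randomization measurement, in an unblinded behavioural trial, with no stated safeguard against knowledge of group. The order of events is explicit. Two steps are inference: that the allocation may be known during week 1, and that week 1 serves as the accelerometer baseline, which the article never calls it although no other pre-video week exists.

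Neither the size nor the direction of bias can be derived from the documents. Under the stated assumptions, falls of 5 to 10 min leave 61 % to 39 % power with a change score, and 83 % to 74 % with adjustment at a correlation of 0.5. A shift the other way exaggerates the effect. Table 1 itself is arithmetically sound and its sample sizes need no change. This is a worthwhile, inexpensive improvement; it does not show that the trial is invalid. If the allocation is in fact withheld until week 1 ends, one sentence saying so settles the knowledge-of-group concern.

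**What to change.** **Remaining recruits.** Open the envelope only after the seven days of week 1 are recorded, at the end-of-week-1 contact already used to send the video, with a short message to control pairs. Opening it then is better than merely delaying disclosure, because pairs without a usable week 1 can be identified before allocation. If the envelope must be opened at the sampling contact, state who learns the result and that the mother does not learn it until week 1 is complete. Label week 1 as the accelerometer baseline throughout.

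**Pairs already enrolled.** Describe week 1 as post-randomization. Add a sensitivity comparison of week-8 values that neither uses the week-1 value nor requires a valid week-1 record. Report week-1 valid wear and exclusions by arm.

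**Cost.** One extra message per control pair; sample size and video timing are unchanged. Recruitment began in November 2014, so the change creates two enrolment periods with different disclosure timing. Record the period for each pair; it can be adjusted for in the regression. The week-8 comparison gives up the precision that adjustment would bring (80 % against 90 % power at an assumed correlation of 0.5, with no shift), which is acceptable for a sensitivity analysis.

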### Statistical methods

The effects of the intervention will be analyzed in line with the intention-to-treat principle through comparison of the changes in the main outcomes between intervention and control group participants. Level of PA, sedentary time, and body weight will be compared between the intervention and control group. All differences in the afore-mentioned outcomes between groups will be examined via linear regression. If the assumptions of linear regression are violated, ordinal or logistic regression analysis will be used. Non-parametric methods (specifically, the Mann-Whitney *U*-test) will also be used to describe differences between groups if needed. Subgroup analysis within the intervention group will be conducted with the mother’s motivation to exercise with the movement-to-music video program and her musical background as covariates. The intervention group will be split into two classes on the basis of these (dummy) variables. These variables will be used to explain differences in exercise activity between mothers in the intervention group. A significance level of 0.05 will be used for all analysis.

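### Running the trial all year does not adjust for season, and no season term is named for the main regression: a small, avoidable loss of precision

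*Protocol article*

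**What the plan says.** All of the text on season is in the protocol article under Recruitment of the study population and randomization, after Fig. 1. The reason given is "Because season-to-season changes in Finland are large", and the expected consequence is that "seasonal differences in PA levels may present themselves". PA is a primary outcome alongside sedentary behavior. The one response named is that "we have paid attention to this effect by performing the intervention throughout the year". On timing: "The recruitment started in November 2014 and will continue until December 2015".

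The same section describes the allocation: "Randomization was performed for blocks of four participants, in a 2:2 ratio". On the order of entry it says "For allocation of participants, an appointment order list for the NELLI five-year follow-up study is being used", although a few sentences earlier it says that no such list existed.

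The Statistical methods section specifies a "comparison of the changes in the main outcomes between intervention and control group participants" and adds that "All differences in the afore-mentioned outcomes between groups will be examined via linear regression". No season, calendar-time or block term is named. The only covariates named are motivation and musical background, and these belong to a subgroup analysis inside the intervention group.

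**The concern.** The article raises season as a problem and answers it with a design feature that does not adjust for it. The main comparison uses a change from week 1 to week 8, about seven weeks. Over such an interval a pair that starts in autumn and a pair that starts in spring can drift in opposite directions for reasons unrelated to the video program. Enrolling through the year puts both kinds of drift into the sample, where they become variance between pairs.

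Blocks of four filled in calendar order would give each arm nearly the same mix of start dates. The difference between arms is then largely free of season. A regression that ignores start date does not know this: it counts the drift as noise and reports an SE larger than the true sampling variation of the estimate. What is at stake is some precision and power, not the correctness of the estimate.

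**Working it through.** **Inputs from the article.** Sedentary time of 460 min/day, a reduction of 25 or 30 min, SD of 60, 65 or 70 min, alpha 0.05 and power 80 % (Power calculations, Table 1). Measurement in weeks 1 and 8. Blocks of four pairs. Recruitment over about 14 months.

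**Step 1: the plan's own figures.** With the normal approximation, n per group = 2 × (1.960 + 0.842)² × (SD/difference)². For SD 70 and 25 min this is 15.70 × 7.84 = 123.1, so 124. The six rows give 124, 107, 91, 86, 74 and 63, exactly as in Table 1.

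**Step 2: assumptions.** The article gives no seasonal amplitude, and it mentions season for PA only. I assume a yearly cosine of amplitude A min/day in sedentary time, common to all pairs, with start dates spread over the year. I take the Table 1 SD as the SD of the analysed change, with season included. Table 1 sets these SDs beside group means, so this too is an assumption. No SD for PA is given, so the size cannot be worked out for PA.

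**Step 3: formula.** A cosine differenced over 7 of 52 weeks has amplitude 2A·sin(7π/52) = 0.82A and variance (0.82A)²/2 across start dates. The SE without season, relative to the SE with it, is SD / √(SD² − (0.82A)²/2).

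| A (min/day) | Amplitude of change | Seasonal variance | Excess SE, SD 70 | Excess SE, SD 60 |
|---|---|---|---|---|
| 5 | 4.1 | 8.4 | 0.1 % | 0.1 % |
| 15 | 12.3 | 75.8 | 0.8 % | 1.1 % |
| 30 | 24.6 | 303.2 | 3.2 % | 4.5 % |
| 40 | 32.8 | 539.0 | 6.0 % | 8.4 % |

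Example, A = 30 and SD 70: 70 / √(4900 − 303.2) = 70 / 67.8 = 1.032.

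If the week 8 level were analysed instead of the change, the seasonal variance would be A²/2. The excess at SD 70 would then be 1.2, 4.9 and 9.3 % for A = 15, 30 and 40.

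**Step 4: simulation.** 4000 trials, 62 blocks of four in time order (124 pairs per group), change score, true reduction 25 min. Here season is added on top of a residual SD of 70.

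| A | Season terms | Mean estimate | Empirical SD | Mean model SE | Power |
|---|---|---|---|---|---|
| 15 | no | −25.24 | 8.85 | 8.97 | 0.802 |
| 15 | yes | −25.24 | 8.85 | 8.90 | 0.807 |
| 30 | no | −24.84 | 8.82 | 9.15 | 0.781 |
| 30 | yes | −24.84 | 8.82 | 8.88 | 0.802 |

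The two models give the same estimate with the same sampling SD. Only the reported SE differs: 9.15 / 8.88 = 1.03 at A = 30. With no true effect and A = 30, the rejection rates were 0.047 without and 0.053 with season terms. Each lies about one Monte Carlo standard error from 0.05, since √(0.05 × 0.95 / 4000) = 0.0034.

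**The case against.** The strongest objection is that the point rests on silence. The article does not list the covariates of the main model and does not say that the model is unadjusted. A condensed article commonly leaves that list to an analysis plan, and none is shown here. This stands: a reader might infer that season is excluded, but the text supports only that no season term is named. The t-test under Power calculations is a sizing assumption and does not settle the matter. What survives is that the article itself raises season and offers year-round running as its answer, which does not do the work of adjustment.

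A reader might also take the article to claim that season is controlled. It says only that attention was paid to it. Year-round running does have a use: the result does not rest on one season.

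Two stronger readings fail. The first is that season biases the comparison. Randomization prevents that, and blocks in time order tighten the balance further. The second is that the loss is large, with a test well below its nominal level. That would need amplitudes of around 45 to 60 min/day, a swing of 90 to 120 min between peak and trough around a mean of 460 min. Nothing in the article supports such a swing, and the simulated test level at 30 min/day is close to 0.05.

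Finally, the premise of time-ordered blocks is reasonable but not clean, because the article both denies and affirms an appointment order list. If the blocks did not follow calendar time, the unadjusted SE would be closer to correct rather than conservative, but seasonal variance would remain in it and the covariate would still help.

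**Conclusion.** The point holds as a minor matter of precision. Year-round running is not an adjustment for season, and a main regression without a season or time term would leave seasonal drift in the residual. The estimate stays unbiased and the error is on the conservative side.

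The size depends wholly on an assumed amplitude and on the cosine model. It is negligible if season moves sedentary time by 15 min/day or less, and worth having at 30 to 40 min/day, where about two points of power are at stake in the simulated case of 30 min/day.

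A reader might infer that the sample size is wrong or that the trial is short of pairs. Neither follows. Table 1 reproduces, and the expected 251 to 335 pairs, about 125 to 167 per group, meet its largest requirement of 124 before loss to follow-up.

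**What to change.** In Statistical methods, or in the analysis plan if one exists, state that the main linear regression for sedentary time and PA includes season of start as a fixed covariate. Calendar quarter of start costs three degrees of freedom; a sine and cosine of the start date cost two. Fix the form before outcome data are examined, so that it cannot be chosen on the results. If the analysis plan already contains such a term, a cross-reference is enough.

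In Recruitment of the study population and randomization, reconcile the statement that there was no appointment order list with the statement that one is being used, and say whether blocks were filled in calendar order.

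The cost is a sentence or two and one covariate. Each pair's start date should already be on file from the baseline contact and the first accelerometer week. No change to sample size or conduct is needed.
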